### Design

2.1

This study is a prospective, assessor-blinded, randomized controlled trial. A total of 96 participants will be recruited at the Zhejiang Provincial Hospital of Traditional Chinese Medicine. Participants will be randomly assigned to either the experimental group or the control group in a 1: 1 ratio. The trial will consist of a 4-week intervention period followed by a 6-month follow-up period. The flowchart of the research procedure is shown in Figure 1. This study will be designed and reported by the Declaration of Helsinki, the Consolidated Standards of Reporting Trials (CONSORT) (24), and the Standards for Reporting Interventions in Controlled Trials of Acupuncture (STRICTA) guidelines (25). Any potential modifications to the protocol that may affect the conduct of the study will be formally documented as amendments. Before such updates are implemented, they will be decided by the project management team and approved by the ethics committee. The trial has been registered with the Chinese Clinical Trial Registry, number ITMCTR2024000328.

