### Randomization, allocation concealment, and blinding

2.4

Eligible patients will be randomly assigned to two groups: the treatment group (receiving warm needle acupuncture combined with Western medicine) and the control group (receiving electro-acupuncture). The randomization will be performed using the CHISS software for block randomization. The size of each block is n. Once the randomization scheme is generated, it will be kept by a third party independent of this study. To ensure allocation concealment, we use sealed opaque envelopes. These envelopes are prepared by an independent member of the research team, and participants draw an envelope randomly upon enrollment in the study to determine their treatment group. Clinical researchers will obtain the specific treatment plan for each patient through designated channels (such as by phone). Assessors will not be informed of the participants’ specific group assignments throughout the follow-up period. All assessment work will be carried out by assessors independent of the treatment process. These assessors will receive rigorous training before the study begins to ensure their standardized understanding and application of the VAS score, thereby ensuring the consistency and accuracy of the assessments. Assessors will be strictly restricted from accessing participants’ treatment group information throughout the follow-up period to maintain assessor blinding. Blind statistical analysis will also be implemented during the data aggregation and analysis phase, with statisticians remaining unaware of the participants’ treatment allocations to ensure the objectivity of the statistical analysis results. In the event of serious adverse events, emergency medical situations, or requests from participants, the sealed envelope containing the blinding information will be opened by an independent third party, and the reasons, time, and personnel involved in the unblinding will be recorded in detail and reported to the relevant committee promptly. Medical decisions will be made based on the unblinding results, and participants will be allowed to withdraw from the trial if necessary.

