### Statistical analysis

2.12

Sample size calculation was performed using PASS software (version 15.0, NCSS LLC). Based on preliminary data, the estimated mean (standard deviation) of the VAS numbness score after intervention for the treatment group (UA + WA) is 1.6 ± 1.0 cm, and for the control group (electroacupuncture) it is 2.41 ± 1.68 cm. To detect a between-group difference of 0.81 cm with 90% power (*β* = 0.10) and a two-sided *α* of 0.05, at least 41 participants are required in each group. Considering a 15% dropout rate, the final sample size is set at 48 participants per group (96 participants in total). This calculation complies with the CONSORT guidelines for randomized controlled trials.

All analyses will follow the intention-to-treat (ITT) principle, including all randomized participants. Additionally, for sensitivity analysis, a per-protocol set (PPS) analysis will be conducted, excluding participants with major protocol deviations (e.g., fewer than 8 acupuncture sessions, and use of prohibited medications). The primary outcome, the change in VAS numbness score over time points (baseline, 1 week, 4 weeks, 12 weeks, 24 weeks), will be assessed using a linear mixed-effects model (LMM). The model will include group, time, group-by-time interaction, and baseline VAS score as fixed effects. Random intercepts and slopes will account for within-individual variability. Missing data will be handled using multiple imputation (MI) with fully conditional specification (FCS) in SAS 9.4 (SAS Institute), generating 10 imputed datasets. Estimates will be combined according to Rubin’s rules. Sensitivity analysis will compare MI with the last observation carried forward (LOCF). For secondary outcomes with continuous variables (e.g., JOA, SF-36), the same LMM structure as the primary outcome will be used. For ordinal/categorical variables (e.g., TCM syndrome score), proportional odds logistic regression or generalized estimating equations (GEE) will be applied to longitudinal ordinal data. For binary outcomes (e.g., adverse events), comparisons between groups will be made using the chi-square test or Fisher’s exact test (for small sample sizes). Risk ratios (RR) and 95% confidence intervals (CI) will be reported.

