The success of assessor blinding will be evaluated using James’ blinding index. A value close to 0.5 indicates effective blinding (0 = completely unblinded; 1 = completely blinded). If there are baseline differences (e.g., age, baseline VAS score), adjustments will be made using analysis of covariance (ANCOVA). Pre-specified subgroups (e.g., age < 50 vs. ≥ 50 years, baseline VAS score severity) will be explored using interaction terms in regression models. *p*-values will be adjusted using the false discovery rate (FDR) correction for multiple comparisons for the primary outcome.

Adverse events (AE) will be graded according to CTCAE v5.0. The incidence rates between groups will be compared using the chi-square test (or Fisher’s exact test for rare events). Descriptive analysis will be conducted for serious adverse events (≥ grade 3). Analyses will be performed using SAS 9.4 (SAS Institute) and SPSS 26.0 (IBM Corp). Continuous outcomes will be reported as mean differences (MD) with 95% CI and effect sizes (Cohen’s d). Categorical outcomes will be reported as risk ratios (RR) with 95% CI. Exact *p*-values will be provided for all tests, with a significance level set at *p* < 0.05 for the primary outcome.

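### Section 2.12 makes closeness to 0.5 the sign of effective blinding on James' index, which contradicts the 0-to-1 scale given in the same sentence

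*Protocol article*

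**What the plan says.** Section 2.4 of the protocol article (Randomization, allocation concealment, and blinding) commits to blinded assessors: "Assessors will not be informed of the participants’ specific group assignments throughout the follow-up period". Section 2.12 (Statistical analysis) names the check: "The success of assessor blinding will be evaluated using James’ blinding index". It then gives the reading in one sentence: "A value close to 0.5 indicates effective blinding (0 = completely unblinded; 1 = completely blinded". The first half of that sentence is the criterion, and the bracket is the scale. The article states no other threshold, no rule based on a confidence interval and no second index.

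**The concern.** The scale rises from no blinding at 0 to full blinding at 1. The criterion picks out the middle of that scale. Taken literally, a result of 1 is as far from the target as a result of 0, so the best possible outcome does not meet the stated sign of success. Conversely, a result in the middle can come from guesses that show clear knowledge of the arm, provided enough other answers are don't know.

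What is at stake is the statement on assessor blinding that the trial will publish. That statement matters mainly for the secondary outcomes in which the assessor takes part (2.8.2): monofilament, pinprick, JOA and electromyography. The arms are easy to tell apart if an assessor sees a session, since one uses moxa on needles and the other electrical stimulation (2.6.1 and 2.6.2). The check is therefore worth getting right.

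**Working it through.** **Inputs from the article.** The index and its reading come from 2.12. Allocation is 1:1 (2.1 Design), and 2.12 gives the size: "the final sample size is set at 48 participants per group (96 participants in total".

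**Assumed.** The article gives no distribution of correct, wrong and don't-know answers. I take one guess per participant, so 48 per arm, and try several patterns.

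**Formula.** James' index is BI = [1 + P + (1 − P)·K]/2. P is the share of don't-know answers. K = (Do − De)/De, where Do is the observed and De the chance-expected disagreement between guess and true arm among the guesses made. With two arms the weight given to a wrong guess cancels; weights of 0.5 and 0.75 gave the same results. Bang's index in an arm is (correct − wrong)/(all answers in that arm), with 0 for random guessing and 1 for all correct.

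**Step 1: reproduce the article's three reference values.**
- All correct: P = 0, K = −1, BI = (1 + 0 − 1)/2 = 0.
- All don't know: P = 1, BI = (1 + 1)/2 = 1.
- Coin-flip guessing, no don't know: P = 0, K = 0, BI = 1/2 = 0.50.

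So the anchors are right, and 0.5 is a true reference value, but only for pure guessing with no don't-know answers.

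**Step 2: well-blinded patterns that are not close to 0.5.** Chance guessing has K = 0, so BI = (1 + P)/2.

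| Don't-know share | BI | Bang, each arm |
|---|---|---|
| 25% | 0.625 | 0 |
| 50% | 0.75 | 0 |
| 75% | 0.875 | 0 |
| 38 of 48 (5 correct, 5 wrong) | (1 + 0.792)/2 = 0.90 | 0 |
| 100% | 1.00 | 0 |

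For the 50% row, simulation with 48 per arm gives a 95% range of about 0.66 to 0.83, which excludes 0.5.

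**Step 3: patterns at 0.5 that are not well blinded.**
- 24 correct and 24 don't know in each arm: P = 0.5, K = −1, BI = (1 + 0.5 − 0.5)/2 = 0.50. Bang is 24/48 = 0.50 in each arm, 95% CI about 0.36 to 0.64.
- 24 correct, 12 wrong, 12 don't know in each arm: P = 0.25, K = (1/3 − 1/2)/(1/2) = −1/3, BI = (1 + 0.25 − 0.25)/2 = 0.50. Bang is (24 − 12)/48 = 0.25.

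The simulated 95% range for half correct and half don't know is about 0.40 to 0.59, the same as for coin-flip guessing without don't-know answers. James' index alone cannot separate the two.

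**Step 4: unblinding in one arm only.**
- No don't-know answers, one arm all correct, the other coin-flipping: P = 0, K = −0.5, BI = 0.25. This is visibly below 0.5, so nothing is hidden.
- One arm 40 correct and 8 don't know, the other 8 correct, 8 wrong and 32 don't know: P = 40/96 = 0.417, K = −0.588, BI = (1 + 0.417 − 0.583 × 0.588)/2 = 0.54. Bang is 40/48 = 0.83 in the first arm and 0 in the second.

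The pooled index hides unblinding in one arm only when don't-know answers are common.

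**The case against.** The strongest reply is that the sentence sets a correct chance reference beside correct anchors and merely joins them badly. It states no rejection rule. An analyst who obtained 0.90 would see that 1 is labelled complete blinding and would hardly declare failure. If the assessors must choose an arm, a value of 1 means that every guess was wrong, and nearness to 0.5 is then a sensible criterion. This stands in part: 0.5 is right for guessing without don't-know answers, and failure of a high value is an inference from the wording. It does not remove the contradiction. The only stated sign of effective blinding excludes the value that the same sentence calls complete blinding.

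A second reply is that don't-know answers offsetting correct guesses is a property of James' index wherever it is used, and no error of this protocol. That is true. It also means that correcting the reading is not enough: a one-sided rule against 0.5 would not flag the table with half correct and half don't know, whose simulated range reaches about 0.59. This is the reason for an arm-level index beside James', and no reason to call the choice of James' index wrong.

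Third, a reader might infer that unblinding in one arm will generally be averaged away. Step 4 does not support that: without don't-know answers such a pattern gives 0.25. Masking needs a large don't-know share, and the article does not say how large that share will be.

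**Conclusion.** The reading in 2.12 contradicts itself and should be corrected. Under the assumed tables it errs in both directions: values of 0.75 and 1.00 from uninformative answers miss the criterion, and a value of 0.50 meets it when every guess made is correct. The sizes rest on guess patterns that I chose, with don't-know shares of 25% or more. With no don't-know answers the stated reference of 0.5 is right.

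A reader might go further and infer that the check will give the wrong verdict in this trial, or that the efficacy result is exposed. The article supports neither. The errors occur in particular patterns, not in every data set. No efficacy model, analysis set or decision in 2.12 depends on the index, and the primary numbness VAS is marked by the patient (2.8.1). The impact is on the credibility of the assessor-blinding statement, mainly for the assessor-administered secondary outcomes. The correction should be made, but it is of modest weight.

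**What to change.** Replace the interpretive sentence in 2.12 with one that says three things: James' index runs from 0 to 1 and higher values mean better blinding; 0.5 is the value expected from random guessing without don't-know answers; and lack of blinding is concluded if the upper 95% confidence limit is below 0.5. Drop closeness to 0.5 as the criterion.

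Because James' index pools the arms and lets don't-know answers offset correct guesses, add Bang's index for each arm with its 95% CI, and report the don't-know share by arm. An interval lying wholly above 0 would point to unblinding in that arm.

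The cost is a few lines of wording and one extra descriptive index from the same guesses, with no new data or participants. Enrolment has begun (2.14 Trial status), so the change should be documented before any guesses are analysed; a reading chosen afterwards would look post hoc.

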#### Inclusion criteria

2.3.1

(1) Age range from 22 to 60 years old; (2) Patients with lumbar disc herniation who underwent PELD surgery and were assessed to have residual numbness symptoms on the first day after surgery; and (3) Numbness with a VAS score greater than 40 mm (score ≥ 40 mm on a 100 mm Visual Analog Scale [VAS]).

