### Sample size

2.5

The VAS score is the primary outcome measure of this trial. Based on the preliminary results from the research team’s earlier trials, the estimated VAS score for the treatment group after intervention is 1.6 ± 1 cm. Based on the data from relevant domestic clinical trials (26) and our preliminary exploratory trials, we predict that the VAS score for the control group is 2.41 ± 1.68 cm. The sample size ratio for the two groups is 1:1. Using PASS15 to calculate the sample size, with a two-sided test set at *α* = 0.05 and *β* = 0.10, and a test power of 0.9, at least 41 participants are needed in each group. Considering a 15% dropout rate, a total of 48 participants will need to be recruited for each group, resulting in a total of 96 participants required.

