### Data collection and management

2.10

After participants sign the informed consent form, researchers will collect personal information such as general demographic information, clinical history, as well as baseline data including the Numbness VAS Score, 10 g Monofilament Test, 40 g Pressure Pinprick Test, JOA Score, Lower Limb Electromyography (H-reflex difference, F-wave conduction velocity, and latency), VAS Score, Traditional Chinese Medicine Syndrome Score, SF-36 (Short Form 36 Health Survey Questionnaire), etc. Outcome measures will be assessed at specified time points and recorded in the CRF. After the trial, two researchers who are not involved in data distribution or outcome assessment will independently extract data from the CRF into an Excel table. A statistician will then perform statistical analysis on this data after careful review and confirmation. To protect participant privacy, personal names will be replaced with a combination of numbers and initials. Researchers shall keep the data confidential for 5 years after the trial termination. To reduce participant dropout rates, researchers will call participants 2 days before treatment to inquire about their condition and encourage them to receive treatment as scheduled.

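### The exploratory test of treatment-by-age effect modification uses age cut at 50 although age in years is available; for a graded effect this loses about 42% of the information if ages are uniform over 22–60

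*Protocol article*

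**What the plan says.** Section 2.12 (Statistical analysis) states: "Pre-specified subgroups (e.g., age < 50 vs. ≥ 50 years, baseline VAS score severity) will be explored using interaction terms in regression models". The age split is given as an example, and it is the only subgroup whose boundary is written out.

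The entry criterion in section 2.3.1 is "Age range from 22 to 60 years old". Age must therefore be established for every patient before enrolment, and section 2.10 adds that "researchers will collect personal information such as general demographic information, clinical history". Section 2.12 also treats age as a possible covariate: "If there are baseline differences (e.g., age, baseline VAS score), adjustments will be made using analysis of covariance (ANCOVA".

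The article gives no expected age distribution, no interaction size and no power for the subgroup analysis. The only effect size and SDs are those behind the main sample size: the post-treatment numbness score "is 1.6 ± 1.0 cm, and for the control group (electroacupuncture) it is 2.41 ± 1.68 cm".

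**The concern.** The plan already fits an interaction term in a regression model, and such a term takes age in years as easily as a two-level indicator. Cutting age at 50 treats a 22-year-old and a 49-year-old as the same, and a 49-year-old and a 50-year-old as different. If benefit rises or falls gradually with age, the cut throws away information. A boundary away from the centre of the sample throws away more.

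At stake is the sensitivity of one exploratory analysis. With 48 patients per arm recruited and about 41 expected to be evaluable, an interaction test is weak from the start, and the cut makes a real gradient harder still to see. The primary comparison and its conclusion do not depend on it.

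**Working it through.** **The plan's own figure.** The article states none for the age analysis, so there is nothing to reproduce on this point. The nearest figure is 41 per group for the main comparison. From the stated inputs ("To detect a between-group difference of 0.81 cm with 90% power (*β* = 0.10) and a two-sided *α* of 0.05", SDs 1.0 and 1.68, 1:1 allocation), n = (1.960 + 1.282)² × (1.0² + 1.68²) / 0.81² = 10.51 × 3.822 / 0.656 = 61.2, that is 62 per group. The stated 41 does not reproduce. That is a separate matter, and nothing below depends on it. I use 41 only as the planned evaluable number per arm.

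**Position of the cut.** (50 − 22) / (60 − 22) = 28/38 = 0.737, about three quarters of the way up. If ages were uniform, 10/38 = 26% of patients would be 50 or older: about 22 of 82, or 25 of 96.

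**Information kept by the cut.** For an effect linear in age, the share of information kept equals the squared correlation between age and the indicator of age ≥ 50. For uniform ages this is 3c(1 − c) with c = 0.737:

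- 3 × 0.737 × 0.263 = 0.58, a loss of about 42%.
- With whole-year ages 22 to 60 equally likely, the loss is 39%.
- A cut at the midpoint of 41 would keep 3 × 0.5 × 0.5 = 0.75, a loss of 25%. So under uniform ages part of the cost comes from dichotomising at all and part from where the boundary sits.

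**Other age distributions on 22–60 (all assumptions).**

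| Assumed ages | Share aged ≥ 50 | Loss |
|---|---|---|
| Truncated normal centred at 41, parent SD 8–15 | 12–22% | 48–62% |
| Truncated normal centred at 48, parent SD 6–15 | 32–36% | 39–42% |
| Truncated normal centred at 50–52, parent SD 6–15 | 34–59% | 33–41% |
| Strongly older-weighted (Beta(2,1), Beta(3,1)) | 46–60% | 34%, 31% |

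**Power.** Inputs: SDs 1.0 and 1.68 cm, 41 per arm, two-sided 0.05, uniform ages (SD 38/√12 = 10.97 years). The interaction size is my assumption.

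- SE of the interaction per SD of age = √((1.0² + 1.68²)/41) = 0.305 cm.
- Benefit rising linearly from 0 at age 22 to 1.62 cm at age 60, averaging the planned 0.81 cm: slope 1.62/38 = 0.0426 cm per year, or 0.468 cm per SD of age.
- Age in years: z = 0.468/0.305 = 1.53; power = Φ(1.53 − 1.96) = 33%.
- Age cut at 50: z = 1.53 × √0.58 = 1.17; power = Φ(1.17 − 1.96) = 21%.
- Direct check of the cut: mean ages below and above 50 are 36 and 55, so the effects differ by 19 × 0.0426 = 0.81 cm. The SE is 0.305 × √(1/0.263 + 1/0.737) = 0.693, which gives the same z of 1.17.
- With all 48 per arm: SE 0.282, z = 1.66 and 1.26, power 38% against 24%.
- With half the gradient (0.81 cm across the whole range, 41 per arm): z = 0.77 and 0.58, power about 12% against 9%, counting both tails.

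These figures use the raw post-treatment SDs. The planned mixed model adjusts for baseline and uses repeated measures, so absolute power may differ. The share of information lost to the cut rests on the age distribution and the linear shape, not on the SDs.

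**The case against.** The strongest reply is that nothing here is wrong. A pre-specified cut tested with an interaction term, rather than by separate p-values within subgroups, is accepted practice. The analysis is called exploratory, the split is listed as an example, and no decision rests on it. All of that stands and limits the point to one of efficiency.

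Four stronger readings are tempting, and the article does not support them:

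- A reader might infer that the cut always costs at least 40%. Without an age distribution there is no such floor. If ages centre at 50–52 the loss can be as low as about 33%, and the boundary then sits near the middle of the sample.
- A reader might fault the plan for giving no reason for 50. A condensed article may leave that to the full protocol or analysis plan, so its absence is no finding.
- A reader might expect a non-significant interaction to be reported as absence of effect modification. The article does not say so.
- A reader might take the 12-point power gap as typical. It belongs to a steep assumed gradient; for 0.81 cm across the range the gap is about 3 points, and both tests are weak.

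The loss is also symmetric. If the effect truly steps at 50 and ages are uniform, the linear term keeps the same 58% and loses the same 42%. Nothing in the article says which shape is likelier. This is why the subgroup estimates should be kept with their intervals. It does not make the cut the better test of a graded effect.

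**Conclusion.** The point holds as a minor one. For effect modification roughly linear in age, cutting at 50 loses about 42% of the information under uniform ages, and roughly 31–62% over the age distributions I think plausible. Samples clustered at younger ages would lose more. Under the assumed 0-to-1.62 cm gradient with 41 per arm, power falls from 33% to 21%; under a 0.81 cm gradient it falls from about 12% to 9%. The conclusion rests on three things that the article does not fix: the shape of any age effect, its size, and the age distribution. Neither version gives a well-powered interaction test, and the primary conclusion is unaffected either way.

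**What to change.** Amend one sentence in section 2.12: test effect modification by age with a group-by-age interaction using age in years, report the estimated treatment effect with 95% CI at a few stated ages, and show the < 50 and ≥ 50 estimates with 95% CIs as a supporting display.

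No new data are needed. Section 2.14 says enrolment is under way, so the change should be recorded through the amendment route in section 2.1 before any comparison by group is seen. The cost is that a linear term is the less efficient test if the effect changes sharply at 50; the retained subgroup estimates would help to show such a step.

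### The trial is sized on one after-treatment comparison at an unadjusted 0.05, but the primary analysis covers several visits with an FDR adjustment and names no deciding contrast

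*Protocol article*

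**What the plan says.** Section 2.5 (Sample size) assumes that "the estimated VAS score for the treatment group after intervention is 1.6 ± 1 cm" and, for electroacupuncture, "we predict that the VAS score for the control group is 2.41 ± 1.68 cm". Section 2.12 (Statistical analysis) repeats these inputs: "To detect a between-group difference of 0.81 cm with 90% power" "and a two-sided *α* of 0.05, at least 41 participants are required in each group", with β = 0.10 given between the two. This is one comparison of two means at an unadjusted 0.05. Neither section names the visit.

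Section 2.12 then describes the analysis as "The primary outcome, the change in VAS numbness score over time points", listing baseline and 1, 4, 12 and 24 weeks. The linear mixed model has group, time, group-by-time and baseline VAS as fixed effects. No term or visit is named as the primary test.

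Later in section 2.12, p-values "will be adjusted using the false discovery rate (FDR) correction for multiple comparisons for the primary outcome". The section closes "with a significance level set at" p < 0.05 for the primary outcome, without saying whether that refers to raw or adjusted p-values.

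**The concern.** The hypothesis that was sized is not the one described for analysis. An FDR adjustment on the primary outcome makes sense only if several primary tests are intended, and each then faces a threshold that can be well below the 0.05 used for sizing. A reader cannot tell which p-value decides superiority.

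The visits also answer different clinical questions. Table 1 runs from the first week of treatment to 24 weeks after it. A trial that showed a difference only at 1 week and one that showed it only at 24 weeks after treatment could both be reported as meeting the primary outcome. At stake are the power of the comparison the trial was built for and the meaning of a positive result.

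**Working it through.** **Inputs.** Means 1.6 and 2.41 cm, SDs 1.0 and 1.68 cm, two-sided 0.05, 90% power, 41 evaluable per group (sections 2.5 and 2.12). Assumed here: the family is the four post-baseline visits, the procedure is Benjamini-Hochberg at 0.05, the sized contrast is the 4-week visit, and test statistics at different visits share a common correlation between 0 and 0.9.

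**1. The plan's own figure.** n per group = (1.960 + 1.282)² × (1.0² + 1.68²) / 0.81² = 10.51 × 3.822 / 0.656 = 61.2, so 62 (63 with Welch's t-test). The stated 41 does not follow from the stated inputs. That is a separate error. It matters here only because it sets the starting power, so results are given from both starting points.

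**2. Power at the unadjusted level.** SE = √(3.822 / 41) = 0.305 cm. Noncentrality = 0.81 / 0.305 = 2.65. Power = Φ(2.653 − 1.960) = 0.756, or 0.743 with Welch.

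**3. Power at the strictest FDR step.** With k comparisons, the smallest p-value, if it stands alone, must reach 0.05/k. The last column starts from the stated 90%, that is, from noncentrality 1.960 + 1.282 = 3.242.

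| k | Strictest step | Critical z | Power, normal | Power, Welch | Power from stated 90% |
|---|---|---|---|---|---|
| 1 | 0.05 | 1.960 | 0.756 | 0.743 | 0.900 |
| 2 | 0.025 | 2.241 | 0.660 | 0.641 | 0.841 |
| 3 | 0.0167 | 2.394 | 0.602 | 0.579 | 0.802 |
| 4 | 0.0125 | 2.498 | 0.562 | 0.537 | 0.772 |

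**4. The full step-up procedure.** FDR relaxes the threshold when other visits also show an effect, so step 3 is the worst case. Simulated power for the 4-week contrast with four visits:

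| True effect | 41 per group (0.756 unadjusted) | From stated 90% |
|---|---|---|
| 4 weeks only | about 0.56-0.57 | about 0.77-0.78 |
| Half as large at other visits (correlation 0.6) | about 0.58-0.59 | about 0.78 |
| Equal at all visits | about 0.70-0.72 | about 0.87-0.89 |

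**5. False claims.** With no effect at any visit, FDR keeps the chance of any claim at about 3.5-5.0% across correlations 0.9 to 0, and the 4-week contrast taken alone is rejected in about 1.4-2.7% of trials. With the trial's assumed effect at one or two visits (noncentrality 2.65), a false claim at another visit occurs in about 5% of trials at correlation 0.6 (5.0-5.1% with one true effect, 4.8% with two), about 6% at correlation 0, and under 4% at 0.9. At correlation 0.6 it reaches 6.3-6.7% only if the true effect is almost certain to be detected (noncentrality about 8).

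**The case against.** The strongest defence is that the article is condensed and refers to a predefined analysis plan, where a list of comparisons would normally sit. The FDR sentence also follows directly on the subgroup interaction tests, so it may be meant for those, and the group-by-time term could be read as one joint test needing no adjustment. Part of this stands: the four-visit family is an inference, and with two or three comparisons the loss is smaller. But the article itself ties the adjustment to the primary outcome, never names a joint test, and sizes on something else. That mismatch lies within the document.

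A reader might go further and infer that the confirmatory error rate is uncontrolled, or that an alpha other than 0.05 is definitely applied. The text does not support either. The section does state p < 0.05. What cannot be determined is whether that is raw or adjusted. With no effect at any visit, FDR keeps the chance of any claim within about 5%, which also limits picking the best visit afterwards. FDR does not guarantee familywise control when some visits have an effect, but at the trial's assumed effect the excess is about 0 to 1 percentage point.

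A reader might also blame the FDR rule for the whole gap between 90% and 54-56%. That is too much: the fall from 90% to about 74-76% comes from the sample size calculation. Two further limits stand. The power figures use raw scores, whereas the planned model adjusts for baseline, which may recover some power. They also use 41 per group, although the intention-to-treat set includes all 96 randomised.

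**Conclusion.** The point holds. The trial is sized on one difference at an unadjusted 0.05, while the analysis places an FDR-adjusted family of unstated size on the primary outcome, fixes no deciding visit or contrast, and has no allowance for the adjustment in the sample size.

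Under the four-visit assumption, the adjustment costs the 4-week contrast about 5 points of power (equal effect at all visits) to about 20 points (effect at that visit only) at 41 per group. From the protocol's stated 90%, it costs about 2 to 13 points. The harms are this lost power and the absence of a fixed visit for the superiority claim; error inflation is a minor matter. The mismatch itself does not depend on any assumption. Its size depends on the number of comparisons, the between-visit correlation and the pattern of effects, none of which the document gives.

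**What to change.** By documented amendment before unblinding (section 2.14 says enrolment has begun), name one primary contrast: the baseline-adjusted between-group difference in numbness VAS from the mixed model at the end-of-treatment (4-week) visit, tested once at two-sided 0.05 without FDR. The 4-week visit is the natural reading of the sizing text, but the sponsor should confirm it. Make the contrasts at 1 week and at 12 and 24 weeks after treatment secondary, and apply any FDR adjustment there, with the comparisons listed.

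The change is to wording only and adds no participants. Its cost is that no confirmatory claim can be made at the other visits. It removes the loss due to FDR but does not restore 90% power, because the shortfall in the 41 per group must be dealt with separately.
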